## Abstract

People with fibromyalgia could experience physical and cognitive impairments. Furthermore, when performing two tasks at the same time, people with fibromyalgia showed a higher dual-task cost compared to a single task than healthy people. This may result in poorer performance of activities of daily living that are commonly presented as a combination of two or more tasks. Transcranial direct current stimulation (tDCS) is a promising nonpharmacological therapy. However, there is controversy regarding the intensities and the effectiveness of this therapy. Thus, the present study will aim: (1) to compare the effectiveness and the impact of two tDCS intensities (1 mA and 2 mA) on cognitive, motor, brain functions, and cardiac autonomic modulation; (2) to study the impact of tDCS on the dual-task performance and creativity after applying tDCS in dorsolateral prefrontal cortex. In this study, 26 women will participate and will be divided into two groups: women with fibromyalgia (*n* = 13), and healthy controls (*n* = 13). A reduction in cognitive-motor interference in dual-task performance is expected, as well as a modification in neurophysiological parameters and an improvement in cardiac autonomic modulation. Lastly, no different effects are expected depending on the stimulation intensity applied. The obtained results will help to determine if tDCS in the dorsolateral prefrontal cortex could improve the occupational performance of women with fibromyalgia.

## 1. Introduction

Fibromyalgia (FM) is characterized by widespread pain and other associated symptoms, including stiffness, fatigue, nonrecovery sleep, anxiety, or depression [1]. On a physical level, people with FM frequently suffer from a sedentary state which reduces cardiovascular fitness and leads to mobility, strength, and balance impairments [2,3,4]. On a cognitive level, people with FM have often impaired cognitive functions such as memory, attention, processing speed, and executive functions [5,6,7]. Furthermore, people with FM have shown an altered brain activity at rest [8,9] and autonomic modulation [10]. As a result of all of these symptoms and their consequences, people with FM have a reduced quality of life [11] and a decreased performance in activities of daily living [12].

Activities of daily living are commonly presented as a combination of two or more tasks at the same time [13,14]. This simultaneous task execution (motor–cognitive, cognitive–cognitive, or motor–motor) is known as the dual-task (DT) paradigm [15]. Previous research has shown that DT leads to an interference that causes a reduction in the performance of one or both tasks [16,17,18]. Regarding people with FM, a decrease in physical performance when two tasks are proposed simultaneously [19,20,21,22] has been observed. The prefrontal cortex (PFC), and particularly the lateral prefrontal cortex (LPFC) are the brain regions for which most interest has been generated, since this structure (LPFC) is mainly involved in coordination, organization, and prioritization processes in DT situations [16,23,24,25,26,27]. 

Different types of pharmacological and nonpharmacological therapies have been used to improve some FM symptoms [28]. Among the nonpharmacological therapies, one alternative therapy of interest is electrical therapy. In this regard, transcranial direct current stimulation (tDCS) is a noninvasive technique that modulates the excitability of the cortex by applying a low-intensity current [29]. This therapy appears to show changes in cortical excitability which persist for one hour when intensities range between 1 to 1.5 mA and the duration is greater 10 min [30]. The methods to apply this technique can be performed during the execution (online) or before the execution of the task (offline), measuring the direct or short/long term effects, respectively [31]. There is currently controversy about the most appropriate type of intensity, since previous studies have compared different intensities showing similar results [32,33,34,35,36,37,38,39]. In addition, higher intensities do not necessarily result in better effects [40,41,42,43]. Moreover, most of the studies have been focused on the primary motor cortex (M1). However, research focused on dorsolateral prefrontal cortex (DLPFC) stimulation has shown benefits in both young [27,44,45,46,47] and healthy older adults [48,49] by reducing the cost and improving the performance of DT.

In FM, the use of tDCS has been mainly focused on treating pain, using anodal stimulation in the motor cortex (M1) [50]. However, fewer studies have focused on applying tDCS to the PFC area and specifically on the DLPFC [51,52,53,54]. On the one hand, these studies have aimed to treat pain and sleep, showing decreased pain but no changes in sleep [51,52,53]. On the other hand, the application of PFC tDCS has been investigated to improve cognitive functions, reporting promising results in short- and long-term episodic memory and executive functions when combined with working memory training [54].

To our knowledge, no studies have focused on the application of tDCS on the DLPFC in people with FM to reduce interference in DT performance. Furthermore, there are no studies that have looked at the effects of different intensities of tDCS on PFC in people with FM in DT performance. Similarly, there are no studies that have focused on describing how neurophysiological variables may be modified in people with FM during DT performance. Therefore, it seems interesting to know how tDCS can influence these types of variables in order to improve the quality of life of this population and to open new frontiers for research.

### Hypothesis and Objectives

The hypotheses that are proposed are as follows: (a) the application of tDCS will improve physical performance in physical variables that will be measured through balance and strength tasks; (b) the application of tDCS will improve performance on neurophysiological variables that will be measured through brain electrical activity and HRV; (c) the application of tDCS will improve performance in DT conditions as well as in creativity tasks; (d) tDCS will have different effects depending on the variability of fibromyalgia symptoms presented (pain, sleep problems and depression; (e) no significant effects on the variables would be expected depending on the type of tDCS intensity applied.

At this point, the main objectives of this study are: (1) to compare the effectiveness and the impact of two tDCS intensities (1 mA and 2 mA) on neurophysiological variables, cognitive and motor functions; (2) to study the impact of tDCS on the dual-task performance and creativity after applying tDCS in the dorsolateral prefrontal cortex.

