#### 2.2.2. Recruitment

Taking into account the results of a previous investigation [56], a sample size of 13 achieves 99% power to detect a mean of paired differences of 3.5 with an estimated standard deviation of differences of 2.5 and with a significance level (alpha) of 0.05 using a two-sided Wilcoxon test assuming that the actual distribution is normal. 

Therefore, the sample will be collected during January/February 2022. One group will be composed of women with FM (*n* = 13) from the local association of persons with fibromyalgia, named AFIBROEX, while the other group will be composed of healthy women (*n* = 13).

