### 2.6. Data Analysis

The outcome results will be included in an anonymous dataset to conduct the statistical analyses. Descriptive and quantitative analyses will be reported. The Statistical Package for the Social Sciences (SPSS, version 24.0; IBM Corp., Armonk, NY, USA) will be employed. Due to the sample size, nonparametric statistical analyses can be the most adequate approach.

In this regard, differences between conditions (1 mA, 2 mA and sham), in all the outcomes, will be analyzed using the Kruskal–Wallis test. Post hoc analyses will be conducted using Mann–Whitney-U tests. Subgroups will be used to study if there are differences in treatment effects according to the presented symptomatology. Furthermore, the [r] effect size will be calculated [95]. Therefore, results will include medians, interquartile ranges, the effect size, and the statistical significance. In order to avoid type I error derived from multiple comparisons, the alpha level of significance will be adjusted according to the Benjamini–Hochberg procedure [96]. 

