## 5. Conclusions

This study will be the first to evaluate the effectiveness of tDCS at the PFC in women with FM, as an alternative to reduce cognitive–motor interference in DT conditions, as well as to modify neurophysiological parameters at EEG and autonomic modulation. In this regard, we hypothesized that tDCS would reduce cognitive–motor interference during DT in women with FM. Furthermore, modification of neurophysiological parameters such as HRV or EEG power spectrum (mainly beta and alpha power) are also expected. The study will dilucidate whether the effects differ depending on the stimulation intensity applied (1 mA and 2 mA).

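### Hypothesis (e), no effect of intensity, can be supported under the stated plan only by a non-significant difference test, which is not evidence that 1 mA and 2 mA act alike

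*Protocol article*

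**What the plan says.** Hypothesis (e), under Hypothesis and Objectives, reads: "e) no significant effects on the variables would be expected depending on the type of tDCS intensity applied". The Abstract repeats the expectation: "Lastly, no different effects are expected depending on the stimulation intensity applied". The first main objective is "to compare the effectiveness and the impact of two tDCS intensities (1 mA and 2 mA) on neurophysiological variables, cognitive and motor functions", and section 5 promises: "The study will dilucidate whether the effects differ depending on the stimulation intensity applied (1 mA and 2 mA".

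Section 2.6 (Data Analysis) gives one inferential route for all outcomes. It is a Kruskal–Wallis test across the three conditions, and then: "Post hoc analyses will be conducted using Mann–Whitney-U tests". Significance levels are adjusted by Benjamini–Hochberg. Reporting consists of medians, interquartile ranges, the effect size r and statistical significance. The section names no equivalence margin, equivalence test or confidence interval, and does not say whether the two groups of 13 are analysed separately or together.

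The sample size (section 2.2.2) is set for detection: "a sample size of 13 achieves 99% power to detect a mean of paired differences of 3.5". The SD assumed for those differences is 2.5, and the calculation uses "a significance level (alpha) of 0.05 using a two-sided Wilcoxon test".

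**The concern.** Most trials hope to reject the null, so low power works against the investigators' hypothesis. Here one of the stated hypotheses is the null, and it is worded in terms of significance. Small numbers, a test that ignores the crossover pairing, and an adjusted alpha each make a non-significant 1 v 2 mA result more likely. Each therefore makes (e) look more credible, whatever the truth.

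The article presents the choice of intensity as an open controversy that the trial will inform. A p-value above the threshold, reported against a hypothesis of no significant effect, could enter that debate as support for similar effects when the data only fail to settle the question.

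**Working it through.** **Inputs from the article.** n = 13 per group, 26 in all; SD of paired differences 2.5; planning difference 3.5; two-sided alpha 0.05 (Abstract and section 2.2.2).

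**Assumptions, not in the article.**
- The SD of 2.5 applies to the 1 v 2 mA contrast. The outcome behind 3.5 and 2.5 is not named.
- The true 1 v 2 mA difference is 1.5, for illustration only. The article defines no material difference.
- The within-woman correlation ρ lies between 0 and 0.8.
- Data are normal, and no Benjamini–Hochberg adjustment is applied.

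**1. The plan's own figure.** The standardised effect is 3.5/2.5 = 1.4. For the Wilcoxon test the effective n is 13 × 3/π = 12.4, and noncentral-t power is 99.4%. Simulation of the signed-rank test also gives 99.4%. The stated 99% reproduces, but for a difference of 1.4 SD.

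**2. What a non-significant paired result leaves open.**
- n = 13: 95% CI half-width = t(12, 0.975) × 2.5/√13 = 2.179 × 0.693 = 1.51.
- n = 26: 2.060 × 0.490 = 1.01.

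With 13 women, a result just short of significance has an interval reaching about 2 × 1.51 = 3.02, which is 3.02/3.5 = 86% of the planning difference. Even an estimate of zero leaves differences of about 1.5 possible.

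**3. Miss rate of a paired t test** (noncentral t, effect = difference/2.5).

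| True difference | n = 13 | n = 26 |
|---|---|---|
| 1.0 | 74% | 50% |
| 1.5 | 49% | 16% |
| 1.75 | 36% | 7% |
| 3.5 | 0.4% | <0.1% |

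**4. Miss rate of the planned Mann–Whitney test.** This test uses the between-woman spread, so the SD of a single measurement matters: SD = 2.5/√(2(1 − ρ)). Simulated values are good to about one percentage point.

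| ρ | SD | Difference 1.5, n = 13 | Difference 1.5, n = 26 | Difference 3.5, n = 13 |
|---|---|---|---|---|
| 0 | 1.77 | 49–50% | 17–18% | 0.4% |
| 0.3 | 2.11 | 64% | 29% | 1–2% |
| 0.5 | 2.50 | 77% | 44–45% | 4–5% |
| 0.7 | 3.23 | 91% | 72% | 18–19% |
| 0.8 | 3.95 | 97% | 88–89% | 39–41% |

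Requiring a significant Kruskal–Wallis test first, or applying Benjamini–Hochberg, cannot lower these rates.

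**5. What showing similarity would take.** Power of two one-sided 5% tests on the paired difference, with a true difference of 0 and n = 13, is 54%, 72% and 92% for assumed margins of 1.75, 2.0 and 2.5.

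**The case against.** The strongest reply is that no section states the decision rule. Hypothesis (e) and the Abstract record expectations, objective 1 is a comparison, and section 5 leaves open whether the effects differ. A reader might infer that the trial will conclude no difference, or declare the two intensities interchangeable. The documents do not say that, and nowhere claim equivalence or non-inferiority. This stands. What remains is that (e) is worded as an absence of significant effects, and the stated analysis gives no other way to support it.

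Second, thirteen women may be the wrong number. All 26 receive every condition, and section 2.6 does not exclude pooling. Pooling cuts the paired miss rate at 1.5 from 49% to 16%. This also stands, so both cases are shown. It does not supply a margin or an interval.

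Third, 1.5 is almost exactly the half-width with 13 women, so a miss rate near one half follows nearly by construction. That is fair. The figure illustrates and does not define a material difference, which is why other differences are tabulated.

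Fourth, the upper Mann–Whitney figures mostly measure the cost of an unpaired test in a crossover, which is a separate defect. That is true. The paired figures show what is left once it is removed.

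Finally, medians, interquartile ranges and r will be reported, so readers would see more than a p-value. None of these gives the precision of the within-woman 1 v 2 mA difference.

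**Conclusion.** The point holds in this form: (e) predicts no significant effect of intensity, the only stated analysis is a difference test with no margin or interval, and so (e) can gain support only from non-significance. That logical gap does not depend on any assumed number.

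Its practical size does. At an illustrative difference of 1.5, with SD of differences 2.5, a paired test would miss it 49% of the time (13 women) or 16% (26 pooled). The planned Mann–Whitney test would miss it about 50–97% or 17–89% of the time, for correlations of 0 to 0.8. The stronger reading, that the plan would overlook any real difference, is not supported. With 13 women a difference of 3.5 is missed 0.4% of the time by a paired test, and about 5% and 19% by Mann–Whitney at correlations 0.5 and 0.7.

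This should be fixed before analysis. It concerns how one hypothesis is judged and reported, and it does not invalidate the randomised comparisons.

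**What to change.** Recast (e) as estimation. For the 1 v 2 mA contrast, report the paired within-woman difference with its 95% CI alongside the effect size. State whether the fibromyalgia and healthy groups are analysed separately or pooled, and state that a non-significant result will not be read as similar effect.

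Only if the sponsor wants to claim similarity: name one outcome and a justified margin in advance, and require the paired 90% CI to lie inside it. This takes more work, because section 2.5.2 lists many primary outcomes and singles out none. With 13 women it may also be underpowered unless the margin is wide.

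The estimation route costs about a paragraph and no extra participants. Its downside is that the intensity result may have to be reported as inconclusive.

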## 2. Materials and Methods

### 2.1. Study Design

This study is a double-blind, sham-controlled, crossover study. All participants will randomly participate through all conditions (1 mA, 2 mA, and sham). This study, in order to fulfil correctly the items of the standard protocol for clinical trials, has followed the SPIRIT 2013 Statement Items [55].

### 2.2. Participants

#### 2.2.1. Eligibility Criteria 

Participants will have to meet the following inclusion criteria to be part of the study: (a) female between 30–75 years of age; (b) be able to communicate with the research staff; (c) have read, understood, and signed the informed consent form. In addition, women with FM must have been diagnosed by a rheumatologist, according to the American College of Rheumatology criteria [1]. The exclusion criteria will be: (a) psychiatric or neurological disorders; (b) pharmacological treatment for anxiety or depression; (c) substance abuse or dependence; (d) contraindication for physical effort; (e) difficulty maintaining balance; (f) leg injury that interferes with flexion and extension of the knee; and (g) being pregnant.

#### 2.2.2. Recruitment

Taking into account the results of a previous investigation [56], a sample size of 13 achieves 99% power to detect a mean of paired differences of 3.5 with an estimated standard deviation of differences of 2.5 and with a significance level (alpha) of 0.05 using a two-sided Wilcoxon test assuming that the actual distribution is normal. 

Therefore, the sample will be collected during January/February 2022. One group will be composed of women with FM (*n* = 13) from the local association of persons with fibromyalgia, named AFIBROEX, while the other group will be composed of healthy women (*n* = 13).

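### The stated 99% power is for one paired test of two conditions at alpha 0.05, not for the planned unpaired three-condition analysis with a Benjamini–Hochberg-adjusted alpha

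*Protocol article*

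**What the plan says.** The design is a crossover. Section 2.1 states: "All participants will randomly participate through all conditions (1 mA, 2 mA, and sham".

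The sample size in section 2.2.2 rests on one calculation: "a sample size of 13 achieves 99% power to detect a mean of paired differences of 3.5". The SD assumed for those differences is 2.5. The test behind the figure is specified as follows: "significance level (alpha) of 0.05 using a two-sided Wilcoxon test assuming that the actual distribution is normal". The outcome measured by 3.5 and 2.5 is not named there; the section refers to a previous investigation. Each of the two groups, fibromyalgia and healthy, has 13 women.

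Section 2.6 says that "differences between conditions (1 mA, 2 mA and sham), in all the outcomes, will be analyzed using the Kruskal–Wallis test", with Mann–Whitney U as the post hoc test. It then says that "the alpha level of significance will be adjusted according to the Benjamini–Hochberg procedure". It does not say which set of comparisons that adjustment covers. Section 2.5.2 lists EEG, HRV, balance, strength, dual-task and creativity measures as primary, and singles out none of them.

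**The concern.** The sizing and the analysis differ in three respects.

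- **Test.** The sizing uses within-woman differences. Kruskal–Wallis and Mann–Whitney treat the conditions as if they came from different women.
- **Number of conditions.** The sizing has one pair of conditions. The analysis has three conditions and pairwise follow-up.
- **Alpha.** The sizing uses 0.05 unadjusted. The analysis adjusts it.

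A reader who sees 99% power will take a null result as informative. That matters here because hypothesis (e) predicts no effect of stimulation intensity, so a non-significant comparison of 1 mA with 2 mA is the expected result. If the tests ignore the pairing and the threshold is lowered, non-significance may come from the method of analysis and say little about the two intensities.

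**Working it through.** **Inputs from the article.** n = 13 women per group, each in all three conditions; mean paired difference 3.5; SD of paired differences 2.5; two-sided alpha 0.05 (sections 2.1 and 2.2.2). Planned tests: Kruskal–Wallis, then Mann–Whitney, with Benjamini–Hochberg (section 2.6).

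**Assumptions.** Normal data, as in the sizing statement. Equal variance in each condition. Conditions compared within one group of 13. Within-woman correlation ρ between conditions is not given, so it is shown as a range.

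**Step 1: reproduce the stated figure.** The standardised paired effect is 3.5 / 2.5 = 1.4. The exact two-sided signed-rank test with 13 pairs, by simulation, gives 99.4%. A paired t calculation with n reduced for Wilcoxon efficiency, 13 / (π/3) = 12.4, also gives 99.4%. The 99% is reproduced.

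**Step 2: carry the same effect to the planned Mann–Whitney test.** With the SD of differences held at 2.5, the SD within each condition is σ = 2.5 / √(2(1 − ρ)), and the effect as an unpaired test sees it is 3.5 / σ. Power is from the exact 13 v 13 test on simulated correlated data.

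| ρ (assumed) | σ | 3.5 / σ | Power at 0.05 | Power at 0.0167 |
|---|---|---|---|---|
| 0 | 1.77 | 1.98 | 99.6% | 99% |
| 0.5 | 2.50 | 1.40 | 96% | 87% |
| 0.7 | 3.23 | 1.08 | 82% | 60% |
| 0.8 | 3.95 | 0.89 | 60% | 33% |
| 0.9 | 5.59 | 0.63 | 20% | 6% |

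The last column uses 0.05 / 3 = 0.0167, the strictest Benjamini–Hochberg step for the three pairwise contrasts alone. The paired signed-rank test at 0.0167 gives 96%.

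**Step 3: the omnibus test.** With sham at 0 and both active conditions at 3.5, Kruskal–Wallis at 0.05 has power 99.9%, 97%, 81%, 55% and 14% at ρ = 0, 0.5, 0.7, 0.8 and 0.9. With no true difference it rejects in about 0.6% of trials at ρ = 0.5 and 0.1% at ρ = 0.7, against a nominal 5%. Ignoring a positive correlation makes the test too conservative, which is where the power goes. Friedman's test in the same setting has about 98% to 99% power at every ρ in the table, because it uses the pairing.

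**Step 4: larger families.** At the strictest step for 10 tests (0.005) the signed-rank test has 89% power, and for 100 tests (0.0005) 50%. The corresponding Mann–Whitney figures at ρ = 0.5 are about 67% and 31%. These steps bind fully only if a single member of the family has an effect.

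**The case against.** Several points on the other side are sound.

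**The stated 99% is not miscalculated.** The article gives its test, alpha and sidedness openly, and the figure reproduces. A reader might infer an arithmetic error; there is none. The figure belongs to a different analysis.

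**Benjamini–Hochberg is not Bonferroni.** Its threshold rises with the number of true effects, and hypotheses (a) to (c) expect effects in many domains. In a simulation with the signed-rank test, an effect of 1.4 and independent outcomes (an assumption), average power was about 87% if 10% of outcomes were affected, 95% if 25% were and 98% if half were. So 0.0167, 0.005 and 0.0005 are worst-step thresholds.

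**The loss depends on ρ.** At ρ = 0 the unpaired test keeps 99.6% at 0.05, and at 0.5 it still has 96%. If changes from pre to post were analysed, which the article does not say, the correlation between conditions could be lower than for raw values.

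**Two stronger readings fail.** A reader might infer that an effect could be impossible to declare, because 13 pairs cannot give a two-sided signed-rank p below 2 / 2^13 = 0.000244. The planned post hoc test is Mann–Whitney, whose smallest p at 13 v 13 is 2 / C(26,13), about 0.0000002, so that floor does not apply to the plan. A reader might also multiply 19 channels by 6 bands by the tasks and conclude that alpha is adjusted over more than a thousand outcomes. The article does not say that each cell is tested separately. The phrase about all the outcomes describes the Kruskal–Wallis comparison, and the adjustment sentence names no family.

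**Details may sit elsewhere.** A full protocol or analysis plan may define the families. That answers the silence about the family, but not the conflict between the tests and alpha in section 2.2.2 and those in section 2.6, all of which the article states.

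**Conclusion.** The concern holds in this form: the 99% is correct for one two-sided signed-rank comparison of two conditions at unadjusted 0.05, and it is not the power of the analysis described in section 2.6.

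For the sized effect, the planned Mann–Whitney test at 0.05 has between 99.6% power (ρ = 0) and 20% (ρ = 0.9). At the strictest step for three contrasts the range is 99% to 6%. Zero correlation between repeated measures on the same women is implausible, so some loss should be expected. Its size cannot be fixed from the article, which gives neither ρ nor the adjustment family, and no single replacement power can be quoted. The loss grows if the family spans the many listed primary measures and few of them respond.

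The figures rest on normal data, equal variances, 13 women per comparison and an SD of differences held at 2.5. The mismatch between sizing and analysis does not depend on those assumptions.

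**What to change.** 1. In section 2.6, replace Kruskal–Wallis and Mann–Whitney with paired methods: Friedman across the three conditions, then Wilcoxon signed-rank for the pairwise contrasts. The analysis then matches both the crossover and the sizing.
2. In section 2.2.2, tie 3.5 and 2.5 to one named primary outcome and one contrast, tested at 0.05. If they do belong to that outcome, the 99% can stand for that test.
3. Apply Benjamini–Hochberg to the remaining outcomes within declared families.
4. If no single primary outcome and contrast is named, delete the 99% and restate power for the test and adjusted alpha actually used, with the assumed within-woman correlation if the test stays unpaired.

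The cost is rewording and, under item 4, a less favourable stated figure. No extra participants are needed. The choice should be recorded before outcome data are seen.
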